## 4. Discussion

IS is a prevalent health condition that usually appears during adolescence due to the development of the spine that occurs at puberty [1,44]. IS can have a negative impact on psychological wellbeing, quality of life, disability, and physical health status, so early detection and treatment are essential [1,4,5,8]. The brace can be effective in the treatment of IS. However, its efficacy has also been questioned due to low adherence rates [9]. In an effort to improve brace compliance, studies have conducted retrospective assessments to investigate adherence and the factors that may negatively influence it [15]. Unfortunately, this methodology has a limited impact on the safety and effectiveness of treatment because assessment is conducted long after problems have arisen and is based on recall and memory, often leading to bias [17]. Additionally, face-to-face assessments require traveling (sometimes long distances), which increases costs and burden for patients (and their families). Electronic assessments can help overcome the limitations of retrospective face-to-face episodic assessments. Due to the widespread use of web and app-based devices in our daily activities, it seems feasible to integrate these devices into the daily monitoring of IS in adolescent populations. Some web and mobile applications have been used previously in detection of AIS and the assessment of adherence to the brace [25,26]. However, the assessment of the psychological and physical state of the patient, which could explain individual differences in adherence and provides important information for the safety and effectiveness of the treatment, has been never included in the daily monitoring of adolescents with IS.

The present protocol described a feasibility study whose aim is to test the usability, acceptability, and clinical utility of an app-based system for the monitoring of adolescents with IS who use a brace. Specifically, we hope to provide new insights into the feasibility of the app (i.e., app adherence and usability), as well as into its utility in detecting non-compliance with brace (treatment adherence), brace-related side effects like pain and interference in sleep (treatment safety), and psychological distress associated with wearing the brace (i.e., intense unpleasant emotions and poor social support). Regarding feasibility, we expect to find high compliance rates with the app-based monitoring system in the end users. Non-adherence to the app will generate clinical alarms, so the professional will be able to contact the participants to encourage them to interact with the app. For this reason, we expect to find low attrition rates during the study period (90 days). Additionally, in relation to the feasibility results, we anticipate that the participants will be very satisfied with the app in terms of acceptability and usability (i.e., “I needed to learn many things before I could start using the system”). Based on previous similar research [45,46], we also anticipate that the clinicians will be satisfied with the app in terms of perceived utility, low burden, and high intention to use. Regarding the clinical utility of the app, we also hypothesized that the app would allow early detection of low brace adherence, brace-related side effects, and psychological distress associated with brace use. Ultimately, we expect that the early detection of these symptoms with the app-based monitoring system will allow clinicians to quickly detect and solve unwanted events and thus provide safer and more effective treatment. To our knowledge, this is the first study to test the feasibility and clinical utility of telemonitoring adolescents with IS through a multidimensional app.

The present study has some limitations. Regarding the inclusion criteria, only adolescents with a smartphone will participate in the study. Therefore, a small proportion of patients may not be able to participate in the study. According to recent global statistics on smartphones, between 80% and 86% of adolescents between 12 and 17 years old own a smartphone [47,48]. Therefore, sample loss from not owning a smartphone is expected to be low. This information will be recorded and will be considered in the discussion on the feasibility of including this methodology for the monitoring of adolescents with IS. An additional shortcoming lies in the study’s ability to produce reliable findings regarding treatment effectiveness. Since this is a feasibility study and there will be no control group, it will be not possible to establish differences between groups and preliminary data on the clinical utility of the app should be interpreted with caution. However, note that the current study design is the preferred to provide information on the feasibility and potential clinical utility of implementing an app-based device for AIS monitoring. This type of study is important to justify whether a larger-scale randomized controlled trial, which is more expensive and time consuming, should be conducted [49]. Feasibility studies are crucial for novel interventions in general and for medical devices and health technology solutions in particular.

## 5. Conclusions

While we recognize the limitations mentioned above, if the app-based telemonitoring of adolescents with IS leads us to the hypothesized results in terms of feasibility and possible clinical utility, this study will have important clinical implications. Among the novelties of the present study is the implementation of an app-based EMA system for the multidimensional monitoring of adolescents with IS. An advantage of implementing this methodology includes the minimization of problems found in retrospective face-to-face episodic assessments (i.e., recall bias, poor monitoring that could compromise the safety of the treatment, and the burden on the physician associated with the time required for evaluations). Taking recall bias, ecological assessments are known to be more accurate than retrospective ones [17]. Therefore, the information obtained with these assessments is more reliable than that obtained from face-to-face appointments where the reliability of the data depends on the recall capacity of the patients [50]. Regarding treatment safety, the app will automatically detect the clinical alarms and send them to the physicians. Therefore, it will allow for timely detection of adverse brace-related symptoms and prompt management. Consequently, the app-based EMA will allow clinicians to provide more efficient and personalized treatments. Finally, and in relation to the burden of assessment, the app monitoring system will allow doctors to receive alarms passively, without the need to actively call patients at random moments during treatment and without patients having to travel to clinics. In fact, the entire monitoring process, as explained in this text, can be performed in an automated way with very little burden for the professionals.

In short, we hope that this new passive telemonitoring method will reduce the current burden on health care services, as doctors will contact patients only when necessary rather than routinely calling patients to assess their physical and psychological functioning. Last but not least, because alarms will occur on an individual level, treatments will become more personalized as specific responses and adaptations will be possible due to the variety of brace-related physical and psychological dimensions evaluated in the app.

## Figures and Tables

**Figure 1 ijerph-18-07767-f001:**
[figure not shown]
Study timeline.

**Table 1 ijerph-18-07767-t001:** Pre-specified clinical alarms detected by the mobile application.

Domain	Clinical Alarms	Recommendations ^1^
Side effects		
Pressure pain	3 consecutive days	Call the patient
Friction pain	3 consecutive days	Call the patient
Excessive heat/sweating	7 consecutive days	Call the patient
Movement difficulties	3 consecutive days	Call the patient
Teased by peers/relatives	4 consecutive days	Psychoeducation
Pain		
Pain intensity	≥3 during 3 consecutive days	Call the patient
Emotions		
Sadness	5 consecutive days	Psychoeducation
Anxiety	5 consecutive days	Psychoeducation
Anger	5 consecutive days	Psychoeducation
Shame	5 consecutive days	Psychoeducation
Overwhelm	5 consecutive days	Psychoeducation
Frustration	5 consecutive days	Psychoeducation
Interference		
Sleeping	3 consecutive days	Call the patient
Basic movements	3 consecutive days	Call the patient
Relationships (friends)	5 consecutive days	Psychoeducation
Relationships (relatives)	5 consecutive days	Psychoeducation
Leisure activities	5 consecutive days	Psychoeducation
Academic activities	5 consecutive days	Psychoeducation
Mood	5 consecutive days	Psychoeducation
Dressing	5 consecutive days	Psychoeducation
Self-image	5 consecutive days	Psychoeducation
Motivation for going out	3 consecutive days	Psychoeducation
Avoid talking about the brace	≥7 during 7 consecutive days	Psychoeducation
Avoid activities/being with others	≥5 during 5 consecutive days	Psychoeducation
Overall physical discomfort	≥5 during 5 consecutive days	Call the patient
Brace adherence		
Morning only (8–14 h)	7 consecutive days	Call the patient
Afternoon only (14–19 h)	7 consecutive days	Call the patient
Sleeping only (last night)	7 consecutive days	Call the patient
Morning and afternoon only	7 consecutive days	Call the patient
Sleeping and morning	15 consecutive days	Call the patient
Sleeping and afternoon	15 consecutive days	Call the patient
No use of the brace	3 consecutive days	Call the patient
Poor social support		
Friends	5 consecutive days	Psychoeducation
Family	5 consecutive days	Psychoeducation
Teachers	5 consecutive days	Psychoeducation
Other people	5 consecutive days	Psychoeducation

^1^ The physician may change the recommended action according to the patient’s condition.

## Data Availability

Data availability is not applicable to this article as no new data were created or analyzed in this study.

## Appendix A. SPIRIT 2013 Checklist: Recommended Items to Address in a Clinical Trial Protocol and Related Documents

**Section/Item**	**Item Nº**	**Description**	**Addressed on Page Number**
Administrative Information			
Title	1	Descriptive title identifying the study design, population, interventions, and, if applicable, trial acronym	1
Trial registration	2a	Trial identifier and registry name. If not yet registered, name of intended registry	4
	2b	All items from the World Health Organization Trial Registration Data Set	1
Protocol version	3	Date and version identifier	4
Funding	4	Sources and types of financial, material, and other support	11
Roles and responsibilities	5a	Names, affiliations, and roles of protocol contributors	1,11
	5b	Name and contact information for the trial sponsor	11
	5c	Role of study sponsor and funders, if any, in study design; collection, management, analysis, and interpretation of data; writing of the report; and the decision to submit the report for publication, including whether they will have ultimate authority over any of these activities	11
	5d	Composition, roles, and responsibilities of the coordinating center, steering committee, endpoint adjudication committee, data management team, and other individuals or groups overseeing the trial, if applicable	4–5
Introduction			
Background and rationale	6a	Description of research question and justification for undertaking the trial, including summary of relevant studies (published and unpublished) examining benefits and harms for each intervention	1–3
	6b	Explanation for choice of comparators	NA
Objectives	7	Specific objectives or hypotheses	2
Trial design	8	Description of trial design including type of trial (e.g., parallel group, crossover, factorial, single group), allocation ratio, and framework (e.g., superiority, equivalence, noninferiority, exploratory)	4
Methods: Participants, interventions, and outcomes			
Study setting	9	Description of study settings (e.g., community clinic, academic hospital) and list of countries where data will be collected. Reference to where list of study sites can be obtained	4–6
Eligibility criteria	10	Inclusion and exclusion criteria for participants. If applicable, eligibility criteria for study centers and individuals who will perform the interventions (e.g., surgeons, psychotherapists)	4
Interventions	11a	Interventions for each group with sufficient detail to allow replication, including how and when they will be administered	4–7
	11b	Criteria for discontinuing or modifying allocated interventions for a given trial participant (e.g., drug dose change in response to harms, participant request, or improving/worsening disease)	8–9
	11c	Strategies to improve adherence to intervention protocols, and any procedures for monitoring adherence (e.g., drug tablet return, laboratory tests)	5–6,9
	11d	Relevant concomitant care and interventions that are permitted or prohibited during the trial	5–7
Outcomes	12	Primary, secondary, and other outcomes, including the specific measurement variable (e.g., systolic blood pressure), analysis metric (e.g., change from baseline, final value, time to event), method of aggregation (e.g., median, proportion), and time point for each outcome. Explanation of the clinical relevance of chosen efficacy and harm outcomes is strongly recommended	7–8, Appendix D
Participant timeline	13	Time schedule of enrolment, interventions (including any run-ins and washouts), assessments, and visits for participants. A schematic diagram is highly recommended (see Figure 1)	5
Sample size	14	Estimated number of participants needed to achieve study objectives and how it was determined, including clinical and statistical assumptions supporting any sample size calculations	4
Recruitment	15	Strategies for achieving adequate participant enrolment to reach target sample size	4
Methods: Assignment of interventions (for controlled trials)			
Allocation:			
Sequence generation	16a	Method of generating the allocation sequence (e.g., computer-generated random numbers), and list of any factors for stratification. To reduce predictability of a random sequence, details of any planned restriction (e.g., blocking) should be provided in a separate document that is unavailable to those who enroll participants or assign interventions	NA
Allocation concealment mechanism	16b	Mechanism of implementing the allocation sequence (e.g., central telephone; sequentially numbered, opaque, sealed envelopes), describing any steps to conceal the sequence until interventions are assigned	NA
Implementation	16c	Who will generate the allocation sequence, who will enroll participants, and who will assign participants to interventions	4-5
Blinding (masking)	17a	Who will be blinded after assignment to interventions (e.g., trial participants, care providers, outcome assessors, data analysts), and how	NA
	17b	If blinded, circumstances under which unblinding is permissible, and procedure for revealing a participant’s allocated intervention during the trial	NA
Methods: Data collection, management, and analysis			
Data collection methods	18a	Plans for assessment and collection of outcome, baseline, and other trial data, including any related processes to promote data quality (e.g., duplicate measurements, training of assessors) and a description of study instruments (e.g., questionnaires, laboratory tests) along with their reliability and validity, if known. Reference to where data collection forms can be found, if not in the protocol	9
	18b	Plans to promote participant retention and complete follow-up, including list of any outcome data to be collected for participants who discontinue or deviate from intervention protocols	5-7
Data management	19	Plans for data entry, coding, security, and storage, including any related processes to promote data quality (e.g., double data entry; range checks for data values). Reference to where details of data management procedures can be found, if not in the protocol	8-9
Statistical methods	20a	Statistical methods for analyzing primary and secondary outcomes. Reference to where other details of the statistical analysis plan can be found, if not in the protocol	9
	20b	Methods for any additional analyses (e.g., subgroup and adjusted analyses)	NA
	20c	Definition of analysis population relating to protocol non-adherence (e.g., as randomized analysis), and any statistical methods to handle missing data (e.g., multiple imputation)	9
Methods: Monitoring			
Data monitoring	21a	Composition of data monitoring committee (DMC); summary of its role and reporting structure; statement of whether it is independent from the sponsor and competing interests; and reference to where further details about its charter can be found, if not in the protocol. Alternatively, an explanation of why a DMC is not needed	4
	21b	Description of any interim analyses and stopping guidelines, including who will have access to these interim results and make the final decision to terminate the trial	9
Harms	22	Plans for collecting, assessing, reporting, and managing solicited and spontaneously reported adverse events and other unintended effects of trial interventions or trial conduct	6-9
Auditing	23	Frequency and procedures for auditing trial conduct, if any, and whether the process will be independent from investigators and the sponsor	NA
Ethics and dissemination			
Research ethics approval	24	Plans for seeking research ethics committee/institutional review board (REC/IRB) approval	4, 11
Protocol amendments	25	Plans for communicating important protocol modifications (e.g., changes to eligibility criteria, outcomes, analyses) to relevant parties (e.g., investigators, REC/IRBs, trial participants, trial registries, journals, regulators)	8
Consent or assent	26a	Who will obtain informed consent or assent from potential trial participants or authorized surrogates, and how (see Item 32)	4-5
	26b	Additional consent provisions for collection and use of participant data and biological specimens in ancillary studies, if applicable	NA
Confidentiality	27	How personal information about potential and enrolled participants will be collected, shared, and maintained in order to protect confidentiality before, during, and after the trial	8-9
Declaration of interests	28	Financial and other competing interests for principal investigators for the overall trial and each study site	11
Access to data	29	Statement of who will have access to the final trial dataset, and disclosure of contractual agreements that limit such access for investigators	9
Ancillary and post-trial care	30	Provisions, if any, for ancillary and post-trial care, and for compensation to those who suffer harm from trial participation	8-9
Dissemination policy	31a	Plans for investigators and sponsor to communicate trial results to participants, healthcare professionals, the public, and other relevant groups (e.g., via publication, reporting in results databases, or other data sharing arrangements), including any publication restrictions	9
	31b	Authorship eligibility guidelines and any intended use of professional writers	NA
	31c	Plans, if any, for granting public access to the full protocol, participant-level dataset, and statistical code	9
Appendices			
Informed consent materials	32	Model consent form and other related documentation given to participants and authorized surrogates	Appendix B
Biological specimens	33	Plans for collection, laboratory evaluation, and storage of biological specimens for genetic or molecular analysis in the current trial and for future use in ancillary studies, if applicable	NA

## Appendix D. Assessment Protocol

1. **Items in the *Qualtrics* Online Platform**

1.1 Items assessed once, in the baseline assessment

Please select your age (in years)

10 (1)… 18(9)

Please indicate your sex:

Male

Female

Intersexual

Please select the country in which you born

Spain (163)… Zimbabwe (1357)

1.2 Questionnaires administered twice at baseline (before the brace and app use) and at the end of the study (after 3 months of brace and app use):

- Sobberheim Stress Questionnaire (BSSQ brace) [33,34]. It contains eight items assessing psychological stress produced by brace in adolescents with IS (i.e., *I find it hard to show my back in public*”). Response use a 4-points Likert scale (0 = “most stress” to 3 = “least stress”). Total scores range from 0 to 24. Higher total scores indicate less stress. Cut-offs proposed in the original versions are: 0–8 (severe stress), 9–16 (moderate stress), and 17–24 (mild stress) [34].
- Italian Spine Youth Quality Of Life (ISYQOL) [35,36]. The scale is composed of 20 items. Some of them assess quality of life with respect to back problems and can be administered to all patients with spinal deformities (spine health domain = 13 items; “*Despite your back problem, do you life a happy life?*”). The remaining items are specifically designed for patients wearing a brace (brace domain = 7 items; “*It is uncomfortable to wear your brace?*”). Responses use a 3-point Likert scale (0 = “never”; 1 = “sometimes”; 2 = “often”). Items 5, 6, 10, and 13 are reverse coded. Total scores are converted into percentages [35]. Final scores range from 0% to 100%, where higher percentages indicate greater quality of life.
- Scoliosis Research Society-22 (SRS-22) [37,38]. This questionnaire is composed of 22 items that evaluate 5 scoliosis domains, namely function/activity (5 items; “*What is your current level of activity?*”), pain (5 items; “*Which one of the following best describes the amount of pain you have experienced over the last month*”), self-image/appearance (5 items; “*How do you look in clothes?*”), mental health (5 items; “*Have you felt calm and peaceful during the last 6 months?*”), and satisfaction with the treatment (2 items; “*which one of the following best describes your pain medication use for back pain?*”). Response scales range from 1 = “Severe/All of the time/Very unhappy/Bedridden/Very bad/Very often/Very poor/None of the time/Severely/Very unsatisfied/Definitely no” to 5 = “None/None of the time/Very happy/Full activities without restriction/Very good/Never/Very good/All the time/Very satisfied/Definitely yes”. Higher scores indicate better perceived health status.
- Hospital Anxiety and Depression Scale (HADS) [39,40]. The HADS consists of 14 items that assess anxiety (seven items; “*I feel tense or wound up*”) and depression (seven items; “*I still enjoy the things I used to enjoy*”). Each item is rated according to a 4-point Likert scale ranging from 0 = “as much as I always do” to 3 = “not at all”. Total scores range from 0 to 21 and higher scores represent higher anxiety and depressive symptoms. Cut-offs are stablished as follows: 0–7 (non-cases), 8–10 (doubtful case), and 11–21 (definite case) [39].
- System Usability Scale (administered only at the end of the study). The SUS evaluates whether a system is considered to be simple to use and useful (e.g., “*I needed to learn many things before I could start using the system”*). It is responded to according to a 5-point Likert scale (1 = “completely disagree” to 5 = “completely agree”). The score of half of the items has to be reverted so that higher scores indicate higher usability and acceptability. Then total score is multiplied by 2.5 so that final scores range from 0–100.

1.3 Items used to evaluate app acceptability in the clinicians (all item responses have a 0–4 ranging from “Completely disagree” to “Completely agree”)

To what extent the app was useful for IS management?

To what extent the app increases IS treatment safety?

To what extent the app increases IS treatment effectiveness?

To what extent the app gives me comfort when managing IS?

To what extent the app is useful for me as a professional?

To what extent the app can be useful for patients with IS?

To what extent the app with alarms is something I want to use in the future?

To what extent the app without alarms is something I want to use in the future?

To what extent the app alarms impacted daily job burden?

To what extent the app has an impact on burden (help patient downloading the app)?

2. **Items Assessed with the Pain Monitor Mobile Application**

A number of items were adapted from or developed considering well-established questionnaires (e.g., BSSQ, ISYQOL, SRS-22, HADS) in order to assess relevant brace-related domains namely side effects of the brace, avoidance behavior, discomfort, and social support.

Items assessed daily at evening

Please indicate if any of these possible consequences of the brace have been difficult for you to bear TODAY. You may select more than one option: (*Inspired by the SRS-22 and the ISYQOL*)

Pressure pain

Friction pain

Excessive heat/sweating

Movements difficulties

Teasing by peers or relative ones

None of the above have difficult for me today

Please indicate the intensity of your pain TODAY. Indicate the average for the whole day between 0 and 10. (*Inspired by the SRS-22*)

0 No pain ---------10 Extreme pain

Please indicate if you feel some of these intense emotions TODAY due to bracing. You may select more than one option: (*Inspired by the SRS-22 and the HADS*)

Sadness

Anxiety

Anger

Shame

Overwhelm

Frustration

I did not feel any of these emotions intensely because of the brace

Please indicate if brace have interfered you in some of these aspects TODAY. You may select more than one option: (*Inspired by the SRS-22, the ISYQOL, and the BSSQ*)

Sleeping (last night)

Basic movements

Friends’ relationships

Family’ relationships

Leisure activities

Academic activities

Mood

Dressing

Self-image

Motivation for going out (classroom or leaving home)

None of the above have disturbed me today

When have you been able to wear the brace sin you went to bed yesterday? [Item created to assess de degree of nonadherence (mildly vs. severe nonadherent), as recommended by [51]

Only at morning (8–14 h approx)

Only at afternoon (14–19 h approx)

Only for sleeping (last night)

Today at morning and afternoon, but no for sleeping (last night)

Sleeping (last night) and this morning

Sleeping (last night) and this afternoon

Sleeping (last night) and all day

I was not able to wear the brace today

Please indicate how much have you avoided talking about your brace today. Rate from 0 to 10. (*Inspired by the BSSQ*)

0 I have not avoided it at all ------- 10 I have avoided it a lot

Please indicate how much have you avoided doing things you like or being with others to hide your brace today. Rate from 0 to 10 (*Inspired by the BSSQ*)

0 I have not avoided it at all ------- 10 I have avoided it a lot

Indicate from 0 to 10 the degree of discomfort with which you have worn the brace TODAY. (*Inspired by the ISYQOL*)

0 No discomfort ------- 10 Maximum discomfort

Select if you have lacked the support of any of these people regarding your brace TODAY. You may select more than one option: [*Inspired by the ISYQOL and the Brace Beliefs Questionnaire* [52]]

Friends

Family

Teachers

Other people

I felt supported today

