### 2.5. Outcome Measures

Primary outcome measures:The usability and acceptability of the app will be assessed by both patients (end users) and clinicians (relevant stakeholders). In the patients, this is evaluated both objectively and subjectively. To obtain an objective feasibility result, we calculate the adherence with the app by dividing the number of completed assessments by the number of planned evaluations and provide the response rate. To obtain a subjective measure of usability and acceptability, at the end of the study period (3 months after the first use of the app), we administer the System Usability Scale (SUS) [31] using an online survey tool that will be sent by mail (*Qualtrics*).In the clinicians, the acceptability of the new app-based monitoring method is evaluated using an assessment protocol developed for a similar earlier study [16]. As reported in Appendix D, this includes items that are consistent with the technology acceptance model [32], including perceived utility, acceptability, and intended use. This will be evaluated at the end of the study with the *Qualtrics* online survey tool anonymously.

Secondary outcomes measures:

Assessed by the Pain Monitorapplication (all once daily from 7 p.m. to 9 p.m.):
Brace adherence: Ad hoc self-reported item: “When have you been able to wear the brace since you went to bed yesterday?” Response options cover all daily periods (morning only, afternoon only, only for sleeping, or any combination of these). To avoid bias due to socially desirable responses, honesty will be encouraged both during recruitment and in the informed consent.Treatment safety: An ad hoc question has been created including the most frequent side effects of brace use according to the literature [10,12] and the authors’ clinical expertise. These include: pain due to pressure, pain due to friction, excessive heat/sweating, movement difficulties, and being teased by peers or close ones.Clinical alarms: in addition to the assessment of brace adherence and side effects, several items were adapted from validated questionnaires (Appendix D) to assess pain intensity, unpleasant emotions, interference, avoidance, discomfort, and social support daily. Clinical alarms will be automatically generated and sent to the physicians by the app depending on the patients’ responses to these items (Table 1).

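### The SUS scoring rule in Appendix D omits the recode to 0–4, so it contradicts the 0–100 range it states

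*Protocol article*

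**What the plan says.** Section 2.5 (Outcome Measures) places patient usability and acceptability among the primary outcomes. The objective part is the app response rate. For the subjective part, at the end of the study, "we administer the System Usability Scale (SUS) [31] using an online survey tool that will be sent by mail". No other subjective patient measure of usability is named.

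The scoring is given in Appendix D, part 1.2, in three steps:

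- Response coding: "It is responded to according to a 5-point Likert scale (1 = “completely disagree” to 5 = “completely agree".
- Reversal: "The score of half of the items has to be reverted so that higher scores indicate higher usability and acceptability".
- Scaling: "Then total score is multiplied by 2.5 so that final scores range from 0–100".

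The entry does not give the number of items, does not define the reversal formula, and does not mention subtracting 1 from each item or any other move to a 0–4 coding. No other part of the article supplies that step.

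Section 3 (Data Plan Analyses) reports the primary outcomes descriptively, with means, standard deviations and frequencies.

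**The concern.** The article states both a scoring algorithm and the range it should produce, and the two do not agree. Reversal changes the direction of a 1–5 item but does not move its lowest value to 0, so a total built from such items cannot start at 0.

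This matters more here than it would in a controlled trial. Section 2 describes a single-group design. A constant error in a score cancels in a between-group difference, but here the absolute level of the mean is itself the result. An upward shift would also favour the expectation in Section 4 (Discussion) that patients will be satisfied with the app, and Section 4 presents studies of this type as a basis for deciding on a larger randomized trial.

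Section 3 has two researchers run the analyses separately. If both follow the written steps, both get the same wrong value. If only one of them recodes, their means will differ by a fixed amount.

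**Working it through.** **Inputs, all from the SUS entry in Appendix D**

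- Response coding: 1 to 5.
- Half of the items reversed; formula not stated.
- Multiplier: 2.5.
- Stated final range: 0–100.
- Number of items k: not stated, so it has to be inferred.

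**Step 1. Implied number of items.** Each item spans 5 − 1 = 4 points, whether coded 1–5 or 0–4. The width of the final range is therefore 2.5 × 4 × k. Setting this to 100 gives k = 100 / (2.5 × 4) = 10.

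**Step 2. Can the written rule give 0–100?** With ordinary reversal (6 − x), every item still runs from 1 to 5. The final score then runs from 2.5 × k × 1 = 2.5k to 2.5 × k × 5 = 12.5k.

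- k = 10: 25 to 125.
- k = 8, the only count that gives a maximum of 100: 20 to 100.
- Any k: the minimum 2.5k is above 0.

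The stated range is not reproduced for any number of items.

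**Step 3. A more generous reading of the reversal.** Suppose the reversed half is scored 5 − x (0–4) and the other half stays at 1–5. With k = 10:

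- Minimum: 2.5 × (5 × 1 + 5 × 0) = 12.5.
- Maximum: 2.5 × (5 × 5 + 5 × 4) = 112.5.

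This is still not 0–100.

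**Step 4. Adding the recode.** Score positively worded items as x − 1 and negatively worded items as 5 − x. Each item is then 0–4, ten items sum to 0–40, and the final score runs from 2.5 × 0 = 0 to 2.5 × 40 = 100. This is the range the article states.

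**Step 5. Size of the difference per patient.**

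- Under 6 − x, a direct item exceeds its recoded value by x − (x − 1) = 1, and a reversed item by (6 − x) − (5 − x) = 1. Over ten items the excess is 10 × 1 × 2.5 = 25 points, whatever the answers. A check on 10,000 simulated response sets gave exactly 25.0 each time.
- Under 5 − x for the reversed half only, the five direct items carry the excess: 5 × 1 × 2.5 = 12.5 points.

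| Scoring (k = 10) | Range | All-neutral respondent | Excess |
|---|---|---|---|
| Recoded to 0–4 | 0–100 | 50 | 0 |
| As written, reversal 6 − x | 25–125 | 75 | 25 |
| As written, reversed half 5 − x | 12.5–112.5 | 62.5 | 12.5 |

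**Step 6. What a constant shift leaves alone.** Adding the same number to every score leaves the SD unchanged, as well as any difference between subgroups such as completers and non-completers. Only the level moves.

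**Comparison with other scales in the same appendix.** The BSSQ-Brace range is consistent with its coding (8 items × 3 = 24), and so is each HADS subscale (7 × 3 = 21). The clinician items are coded 0–4 explicitly.

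**The case against.** The strongest reply is that this is a shortened description of a published instrument, for which Section 2.5 cites a source. Appendix D does not set out full scoring elsewhere either: it leaves the ISYQOL percentage conversion to a citation and gives no formula for the SRS-22. An analyst who reads the whole SUS sentence sees the 0–100 range and can work back to a 0–40 sum. This is fair as evidence of intent. It does not remove the point, because the article does not leave the SUS rule to the source; it states a rule and the resulting range, and the two disagree.

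A reader might infer that the primary usability outcome will be reported 25 points too high. The documents do not support that. No Qualtrics set-up or analysis code is shown, and the excess arises only if the steps are applied literally. The figure of 25 also needs ten items, a number inferred by taking the stated range width as correct, and 6 − x reversal, which the article does not define.

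The consequences are limited in other ways, and these stand:

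- No SUS threshold, go/no-go rule or sample size argument uses the score.
- The response rate and the clinician items, which are also part of the primary outcome, are untouched.
- The error could be corrected later from the item responses.
- It would sometimes show itself: under 6 − x, a correct score above 75 becomes a value above 100. That safeguard is partial, since a correct score of 75 or less stays within 100 and a range check would not flag it.

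**Conclusion.** The contradiction is real and internal to the SUS entry: the written steps cannot produce a minimum of 0 under either reading of the reversal or for any number of items. What is missing is the recode of each item to 0–4.

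The size is conditional. If the rule is applied literally to ten items, every score and the mean are 25 points too high with 6 − x reversal, or 12.5 points too high if only the reversed half is scored 5 − x. The effect would fall on the reported level and on any reading of it against a 0–100 scale. This is an incomplete scoring rule for the patients' only subjective primary measure, worth correcting because the absolute mean is what the study reports. It is not evidence that the outcome has been or will be mis-scored.

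**What to change.** Replace the scoring sentences in the SUS entry of Appendix D with an explicit rule: recode each item to 0–4 (response minus 1 for positively worded items, 5 minus response for negatively worded items), sum the ten items to 0–40, and multiply by 2.5 to obtain 0–100. State the number of items and which ones are negatively worded.

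Check any automatic scoring in Qualtrics and the code of both analysts against this rule. Two test records are enough: all responses at 3 must give 50, and the least favourable response to every item must give 0.

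The cost is one rewritten sentence and a code check. No new data are needed, and the sample size is unaffected.
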